## Abstract

**Introduction::**

Lumbar spinal stenosis (LSS) is a pathological condition that causes a variety of neurological symptoms due to narrowing of the anatomical structures; usually, conservative treatment is recommended, rather than surgical treatment. Acupotomy combines conventional acupuncture with small scalpels; the procedure can be considered minimally invasive, and has recently received considerable attention in clinical practice. Still, there is a lack of data and randomized controlled trials regarding acupotomy related to LSS. Additional studies are necessary, considering the low methodological quality and small size of the study.

**Methods and analysis::**

This is a pragmatic, pilot, randomized controlled trial. The trial comprises 8 weeks of treatment, with 16 visits and a 4-week follow-up period. Forty participants diagnosed with LSS will be randomly assigned to either the experimental or control groups; both groups will receive acupuncture and interferential current therapy twice a week for 8 weeks, while the experimental group will receive an additional acupotomy intervention once a week for 8 weeks. The primary outcome will be assessed using the visual analog scale; the secondary outcome will be measured by self-rated walking distance, Oswestry Disability Index, and short-form McGill Pain Questionnaire. Measurements will be obtained prior to the start of the clinical trial, 4 weeks after the interventional procedure, 8 weeks after the procedure, and 4 weeks after the end of the interventional procedure. Blood tests and adverse reactions will be performed to ensure safety of the treatments.

**Conclusion::**

We expect that this study will provide basic data for future large-scale acupotomy studies regarding LSS.

## Introduction

1

Lumbar spinal stenosis (LSS) is a pathological state that causes a variety of neurological symptoms. Narrowness of the spinal canal, root canal, or intervertebral foramen—caused by bulging discs, hypertrophy of surrounding bones, and overgrowth of soft tissue that damages the nerve and vascular components—can also cause neurological symptoms.^[1]^ LSS may present as low back pain, hip pain, and lower extremity pain caused by walking, standing, or stretching; other symptoms include discomfort, sensory loss, and weakness of the lower extremities.^[2]^

Exercise, medication, epidural steroid injections, physical therapy, and surgery are well-known treatments for LSS.^[3–6]^ Generally, conservative treatment is recommended, rather than surgical treatment. Although many patients undergo multiple conservative treatments for LSS repeatedly, they often experience the associated symptoms and eventually require surgical treatments such as nerve decompression and spinal fusion. However, patients often experience postsurgical complications and lower satisfaction after these surgical treatments^[7]^; therefore, patients try to find safer and more effective conservative treatments—including acupuncture—for LSS treatment.^[8,9]^ Acupuncture—supported by compelling evidence as an appropriate treatment for chronic pain—is an effective complementary alternative to treatment for spinal stenosis.^[10]^ Consequently, many studies have recently been conducted regarding the various forms of acupuncture, including acupotomy and thread embedding acupuncture, designed to enhance the effectiveness of acupuncture.^[11,12]^

Acupotomy—a type of acupuncture that combines conventional acupuncture with a small scalpel—has recently garnered attention, and can be considered minimally invasive.^[13]^ Acupotomy has received considerable attention in clinical practice; however, there is a lack of data and randomized controlled trials (RCTs) regarding acupotomy related to LSS. Additional studies are necessary considering the low methodological quality and small size of the study.^[14]^ Therefore, we plan to conduct an RCT to evaluate the effectiveness of pain reduction, improvement in quality of life, and safety of acupotomy in patients with LSS.

## Materials and methods

2

### Study design

2.1

This is a pragmatic, pilot, RCT, approved by the Daegu Oriental Hospital of Daegu Haany University Clinical Trial Review Committee (DHUMC-D-21001-ANS-01) and registered with the CRIS (KCT0006234). This report complies with the Consolidated Standards of Reporting Trials guidelines. This study protocol complies with the tenets of the Declaration of Helsinki and Korean Good Clinical Practice. The trial comprises 8 weeks of treatment, with 16 visits and a 4-week follow-up period.

### Participants

2.2

Forty participants diagnosed with LSS will be enrolled in this clinical trial; they will be recruited through advertisements posted in hospitals, the hospitals’ webpages, etc. All participants will be provided with a complete explanation of the trial protocol and will receive a written explanation and informed consent form. Each participant has the right to withdraw the clinical trial; participants will be excluded for violating the protocol, not meeting the inclusion criteria, or withdrawing consent.

### Eligibility criteria

2.3

The inclusion criteria are: an age of 50 to 80 years; low back pain or lower extremity pain for at least 3 months; LSS diagnosed by magnetic resonance imaging or computed tomography; a visual analog scale (VAS) score between 4 and 7; no problems with language, expression, and concentration; being able to attend follow-up evaluations during the trial; and voluntarily signing an agreement to participate in the study.

Exclusion criteria are: side effects or a history of hypersensitivity to acupuncture treatment; requiring severe surgical treatment for neurological symptoms of cauda equine syndrome, or sensory or motor paralysis; having undergone spinal surgery prior to the clinical trial; having undergone treatment for epidural nerve block within 3 months of the trial; neuromuscular scoliosis or neurodegenerative diseases; results of liver function tests (alanine aminotransferase, aspartate aminotransferase) exceeding 3 times the normal range; abnormal kidney function test results; a neurological or psychologically important medical history, or a related pre-existing condition; pregnant women, lactating women, and women with plans to conceive or who do not agree with appropriate contraception options; taking anticoagulant medication; use of an artificial pacemaker; any participant regarded as inappropriate by the director of the clinical trial.

### Intervention

2.5

All participants will be randomly assigned to the experimental or control groups, and all treatments will be treated by a Korean medical doctor. Both groups will receive acupuncture and ICT, twice a week for 8 weeks; the experimental group will receive an additional acupotomy intervention once a week for 8 weeks.

#### Acupotomy

2.5.1

Participants will undergo acupotomy with a 0.50 × 50 mm sterile, disposable, stainless steel acupotomy (DongBang Acupuncture Inc., Gyeonggi-do, Republic of Korea). Acupotomy is performed at 7 pre-defined acupoints (the governor vessel at the corresponding level of stenosis in the imaging diagnosis, bilateral Hyeopcheok acupoints, and upper and lower bilateral Hyeopcheok acupoints) without needle retention time. Additionally, hip tender points around GB30 and tender points of the hamstring muscles can be treated, depending on the participants’ needs. When an invasive intervention is needed, it is inserted slowly while also monitoring whether the participants complain of pain in the neural course.

#### Acupuncture

2.5.2

Participants will undergo acupuncture with 0.30 × 0.40 mm and 0.35 × 0.60 disposable, sterilized, stainless steel acupuncture needles (DongBang Acupuncture Inc.) at 17 pre-defined acupoints (GV3, and both sides of BL23, BL24, BL25, BL26, GB30, GB31, BL40, and BL60). Additionally, several acupoints (if the radiating area is up to the buttock, GB29; if the radiating area is up to the thigh, BL36 and BL37; if the radiating area is up to the calf, BL55 and BL57) may be further included, considering the participants’ needs. The acupuncture needles will be inserted to a depth of approximately 50 to 60 mm with electrical stimulation, and BL24 and BL26 will be stimulated by electroacupuncture (ES-160; ItoCo. Ltd., Saitama, Japan) at an intensity of 3 Hz. The retention time will be 20 ± 5 minutes.

#### ICT

2.5.3

ICT (GOODPL Inc., Gangwon-do, Republic of Korea) was performed by attaching 4r parts to the lumbar region of the corresponding level of stenosis in the range of 4000 to 4100 Hz. The intensity (mA) will be set to ensure that the participants do not feel pain, and will be maintained for 15 ± 5 minutes.

### Outcome measurement

2.6

The primary outcome of this study will be assessed using the VAS.^[15]^ Secondary outcomes will be measured by self-rated walking distance, short-form McGill Pain Questionnaire (SF-MPQ),^[16]^ and Oswestry Disability Index (ODI).^[17]^ Measurements will be obtained prior to the start of the clinical trial, 4 weeks after the interventional procedure, 8 weeks after the interventional procedure, and 4 weeks after the end of the interventional procedure. The treatment schedule and outcome assessments are presented in Table 1.

**Table 1 T1:**
[figure not shown]
Schedule of the treatment and outcome assessment.

#### Primary outcome measure

2.6.1

##### VAS

2.6.1.1

The VAS (from 0–10; 0, no pain; 10, worst pain imaginable) is used to measure subjective pain intensity, which cannot be objectively quantified. The participants indicate the point representing their current pain intensity, and the assessors measure the length from the left side of the horizontal line, to the point indicated by the participants.

#### Secondary outcome measures

2.6.2

##### Self-rated walking distance

2.6.2.1

The assessment of self-rated walking distance will be evaluated by the fourth ODI item. In many LSS studies, ODI is measured to investigate the overall function of the patients. The fourth ODI item is also used to quantify individual walking ability, which is known to be the most responsive and valid score of any change in measured walking ability. The fourth ODI item is expressed as a score from 0 to 5; a higher score indicates a lower walking ability.

##### SF-MPQ

2.6.2.2

SF-MPQ is a short form of the existing MPQ, which is widely used to assess the magnitude of pain experienced. Each item consists of 15 adjectives; these represent the sensory and affective magnitude of pain experienced using a descriptive scale, the Present Pain Index (PPI), and VAS. The 15 descriptive scales include 11 sensory and 4 affective words; the words on the descriptive scale are graded on a 4-point scale (0 = no symptoms, 1 = mild, 2 = moderate, or 3 = severe), while the Present Pain Index scale measures the current pain magnitude on a 6-point scale (0 = no pain, 1 = mild, 2 = discomforting, 3 = depressing, 4 = horrible, or 5 = excruciating).

##### ODI

2.6.2.3

The ODI is known to be highly valid for evaluating the general living function of patients with a backache, and was found to be highly reproducible in patients with LSS and neurological claudication. The ODI evaluates 10 ordinary items: pain intensity, personal care, lifting, walking, sitting, standing, sleeping, sex life, social life, and traveling; each everyday activity is graded on a 6-point scale. The scores of all the items answered are summed, divided by the number of items answered, and multiplied by 100; a high score means that the level of disability in daily life due to low back pain is high. The verified Korean version of the ODI will be used in this study.

### Safety

2.7

The safety of this trial will be assessed by the white blood cell count, platelet count, red blood cell count, differential count, hematocrit, hemoglobin level, erythrocyte sedimentation rate, aspartate aminotransferase level, alanine aminotransferase level, blood urea nitrogen level, creatinine level, C-reactive protein, prothrombin time, partial thromboplastin time, serum potassium level, serum sodium level, and serum chloride level. Participants will undergo hematological and blood biochemical tests before, as well as 8 weeks after the procedure, for safety verification.

All adverse events (AEs) and vital signs will be monitored at every visit. In principle, the participants will be asked to immediately report any AEs; if AEs occur during the clinical trial, the association between acupotomy or usual care in clinical trials will be evaluated, and a follow-up investigation conducted.

### Statistical analysis

2.8

Statistical analyses will be conducted on the basis of the Clinical Trial Statistical Guidelines (KFDA, 2000).

SPSS Win. Ver. 26 (IBM, Armonk, NY) will be used for the statistical analyses.

The statistical package used based on the Clinical Trial Statistical Guidelines (KFDA, 2000) was SPSS Win. Ver. 26 (IBM, Armonk, NY). The last observation carried forward method will be used for missing data due to dropouts. The significance level will be set at 5% for statistical significance. Intention-to-treat analysis will be conducted for all data analyses. The study will confirm the clinical characteristics and comparative equivalence of demographic variables between the experimental and control groups. To assess baseline characteristics of quantitative data between groups, the Student *t* test for the parametric method or Mann-Whitney *U* test for the non-parametric method will be used. The chi-squared (χ^2^) test will be used to compare qualitative data between groups. To compare baseline measurements with those obtained at 4, 8, and 12 weeks regarding VAS, self-rated walking distance, SF-MPQ, and ODI, the paired *t* test (parametric method) or Wilcoxon signed-rank test (non-parametric method) will be used; repeated measures analysis of variance will be conducted to evaluate the differences between groups. If the interaction between the group and time is statistically significant, we will investigate the point where the resulting pattern changes between the 2 groups. The χ^2^-test will be used to compare the incidence of AEs associated with the groups and interventions.

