## Discussion

3

Traditionally, there are several approaches to treating LSS, including both conservative and surgical treatment. It has been reported that the cure rate of surgical and non-surgical treatment cannot be stated conclusively, and that the incidence of side effects increases after a surgery.^[18]^ Therefore, there has recently been a growing interest regarding safer and more effective conservative treatments, such as acupuncture and acupotomy, which have been widely used in clinical practice for the treatment of LSS. Recently, various studies have reported the efficacy and safety of acupuncture and acupotomy in LSS.^[19–21]^

According to the China Association of Acupuncture-Moxibustion's back pain guidelines, acupotomy is recommended for pathological changes in muscles, ligaments, and articular capsules in lumbar soft tissue.^[22]^ Based on a systematic review and meta-analysis evaluating the effectiveness of acupotomy in recently published studies, acupotomy could be clinically beneficial as a minimally invasive treatment for LSS.^[21,23]^

Although the methodological quality of the study is poor and the number of good-quality RCTs few, the superiority of acupotomy has been reported in a meta-analysis.^[21]^ While studies on the efficacy of acupotomy are ongoing, there are limitations to the application of these clinical studies in clinical practice. In real clinical situations, combinations of treatments are utilized more often than single treatments for LSS; pragmatic studies allowing for better decision-making regarding combinations of treatments are therefore drawing attention. Nevertheless, pragmatic acupotomy studies on LSS are rare, and making effective clinical decisions for patients with LSS remains a challenge. Therefore, we designed this pilot, pragmatic study to assess the safety and efficacy of acupotomy guidance in patients with LSS. We expect that the results of this study will provide basic data for conducting future, large-scale acupotomy studies on LSS. Additionally, it is possible to establish a basis for comparing and confirming the effects of adding acupotomy to existing clinical treatments.

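### The paired tests against baseline share the 5% level of the between-group analysis and are not labelled descriptive, although they cannot show what acupotomy adds

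*Protocol article*

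**What the plan says.** Section 2.8 (Statistical analysis) sets one threshold for the whole plan: "The significance level will be set at 5% for statistical significance". It then assigns two kinds of analysis to the efficacy outcomes.

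- **Change from baseline.** "To compare baseline measurements with those obtained at 4, 8, and 12 weeks regarding VAS, self-rated walking distance, SF-MPQ, and ODI", a paired t test or a Wilcoxon signed-rank test is to be used. The text does not say whether this is done separately by arm.
- **Difference between arms.** The same sentence goes on: "repeated measures analysis of variance will be conducted to evaluate the differences between groups". The next one adds: "If the interaction between the group and time is statistically significant, we will investigate the point where the resulting pattern changes between the 2 groups".

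Nowhere does the article call the paired tests descriptive or supportive.

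Two other places matter. Section 2.5 (Intervention) says "Both groups will receive acupuncture and ICT, twice a week for 8 weeks", with acupotomy as the addition in one arm. The Discussion describes what the trial can offer as a basis for "comparing and confirming the effects of adding acupotomy to existing clinical treatments".

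**The concern.** The trial asks what acupotomy adds to care that both arms receive. A paired test asks whether an arm differs from its own starting point. With two active treatments given twice a week in both arms, a change from baseline mixes usual care, natural course and expectation with whatever acupotomy contributes. Two design features can add change unrelated to acupotomy. Entry requires a VAS of 4 to 7 (section 2.3), which allows regression to the mean. Participants also know their treatment while rating their own pain (section 2.4).

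The randomised comparison cancels the influences that the arms share, although not a difference in expectation caused by the open design. The paired tests make no use of it. With the same 5% level and no label, a significant paired test in the acupotomy arm, or significance in that arm alone, stands on the page with the same rank as the between-arm result. Read as efficacy, it would mislead the larger studies for which this pilot is meant to supply basic data.

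**Working it through.** The article gives no effect size, SD or power figure, so there is no stated number to reproduce. The check asks how often paired tests would seem to favour acupotomy when it adds nothing.

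**Inputs from the article**
- Total sample: "Forty participants diagnosed with LSS will be enrolled in this clinical trial" (section 2.2). Section 2.4 makes the arms equal in size, so n = 40 / 2 = 20 per arm.
- Significance level 5% (section 2.8). No sidedness is stated; two-sided is assumed.
- Four outcomes and three post-baseline visits (section 2.8).

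**Assumption.** Both arms share the same true standardised change d (mean change divided by the SD of the change), shown over 0.2 to 1.0.

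**Step 1: number of tests.** 4 outcomes × 3 visits = 12. If run in each arm, 12 × 2 = 24.

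**Step 2: chance that one arm's paired t test is significant.** The statistic follows a noncentral t distribution with 19 degrees of freedom and noncentrality d√20. The two-sided critical value is 2.093. Call this chance p.

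**Step 3: chance that only the acupotomy arm is significant.** The arms are independent, so this is p(1 − p). It cannot exceed 0.25, which is reached at p = 0.5.

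| Shared change d | Noncentrality d√20 | p | Only acupotomy arm significant, p(1 − p) |
|---|---|---|---|
| 0.2 | 0.894 | 0.136 | 11.7% |
| 0.3 | 1.342 | 0.247 | 18.6% |
| 0.45 | 2.012 | 0.480 | 25.0% |
| 0.6 | 2.683 | 0.721 | 20.1% |
| 0.75 | 3.354 | 0.889 | 9.9% |
| 0.9 | 4.025 | 0.968 | 3.1% |
| 1.0 | 4.472 | 0.989 | 1.1% |

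**Step 4: comparison.** A two-sided 5% between-arm test would favour acupotomy by chance in 5% / 2 = 2.5% of trials, whatever change the arms share. In simulation of a single-visit between-arm test on VAS change, the two-sided false-positive rate stayed at 4.9% to 5.2%.

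**Step 5: what the table shows.** Arm-wise comparison is most misleading at moderate shared changes. At 1.0 SD its rate falls below 2.5%, but only because both arms are then almost always significant. There the acupotomy arm's own paired test is significant in about 99% of trials although acupotomy adds nothing.

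**Step 6: regression to the mean alone.** With no treatment effect in either arm, the 4 to 7 entry window was simulated under assumed population means of 4.0 to 5.5, SD 2 and correlations of 0.5 or 0.7. The acupotomy arm showed a significant fall in VAS in 2% to 32% of trials. The lower end is what chance alone would give.

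**The case against.** The strongest reply is that section 2.8 gives each method its own task. The paired tests describe the course from baseline. The repeated measures ANOVA, with follow-up of a significant group-by-time interaction, deals with the difference between arms. On this view nothing is missing, and describing change per arm is useful in a pilot. The article is also condensed, so the ranking of analyses may be set out in a fuller document.

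Much of this stands, and it rules out several stronger readings that a reader might infer.

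- **That the trial has no valid test of its question.** The ANOVA is planned in the same sentence as the paired tests.
- **That within-arm results will be presented as benefit, or arm-wise p-values compared.** The article says neither. The rates above measure a risk left open, not a stated plan.
- **That the article itself specifies 24 tests.** It specifies 12 comparisons; running them by arm is an inference, though the natural one.
- **That misleading results would occur in about a fifth to a quarter of cases.** This holds only for assumed changes around the peak of p(1 − p). Over 0.2 to 1.0 SD the range is about 1% to 25%.
- **That a high rate of significance, such as 89% at 0.75 SD, holds whatever acupotomy does.** It holds only if acupotomy adds nothing. If it adds something, that arm's rate changes.

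What the reply does not remove is the stated choice itself. The article fixes hypothesis tests, at the common 5% level, for comparisons that cannot answer the trial's question. Describing the course of each arm needs means and intervals, not p-values.

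**Conclusion.** The point holds in a limited form. The paired tests cannot isolate acupotomy because both arms receive active treatment, and section 2.8 gives them the same significance level as the between-group analysis without marking them as descriptive. The defect lies in their status, not in a missing analysis.

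Its size depends on how the results would be read. Under no acupotomy effect, comparing arm-wise p-values would single out the acupotomy arm in about 1% to 25% of cases per outcome and visit, against 2.5% for a between-arm test. This rests on 20 complete pairs per arm, two-sided paired t tests and an assumed shared change of 0.2 to 1.0 SD; the article supplies no SD or expected change to narrow the range. That the paired tests cannot answer the question does not depend on these assumptions. The weight is minor to moderate.

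**What to change.** In section 2.8:

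1. Replace the paired t and Wilcoxon tests with the mean change from baseline in each arm and its 95% confidence interval, reported descriptively and without p-values.
2. State that efficacy conclusions about acupotomy rest on the between-arm difference, adjusted for the baseline value of the outcome, with its 95% confidence interval. For VAS, name one visit in advance, for example week 8 as the end of treatment, and treat the other visits as supportive.
3. Leave the adverse event comparison as it is. This change concerns the efficacy outcomes only.

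**Cost.** No new data or participants are needed. The within-arm p-values are lost, and the repeated measures analysis has to be re-specified with baseline as a covariate, so this is more than a change of label. The between-arm comparison will also be imprecise: an unadjusted single-visit t test with 20 per arm reaches 80% power only at a standardised difference of about 0.91. The confidence interval shows that imprecision openly, which suits a pilot.
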